Stampacchia *et al.*, 2022). However, its mechanistic effects on NP for individuals with SCI have not been well investigated to date. Only two case studies/series employing robotic-assisted gait were identified in the extant literature that mandated participants have NP in the moderate and severe categories prior to using the exoskeleton and results demonstrated meaningful reductions in pain intensity ratings (
Cruciger *et al.*, 2016;
Kressler *et al.*, 2014). The ExSCIP randomised feasibility trial addresses the current lack of clinical trials in this area, examining exoskeleton-based walking 3 times per week, as a mechanistic-based intervention for NP after SCI. It will test the feasibility and acceptability of an exoskeleton-based walking intervention, and whether it demonstrates positive signals in reduction of NP intensity and interference levels to warrant onward progression to a definitive trial.

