## Methods

### Study design and setting

The ExSCIP study is a single centre, phase 2 randomised, single blinded, feasibility trial, informed by Bowen’s framework for feasibility studies (
Bowen *et al.*, 2009). Given SCI is considered a rare condition, we will apply a randomised feasibility study to allow a better-informed decision on whether to proceed to a larger multi-centre and international trial (
Eldridge *et al.*, 2016). This trial protocol has been registered on clinicaltrials.gov (NCT06463418)
https://clinicaltrials.gov/study/NCT06463418)

Progression criteria are based on consideration of the primary objectives around feasibility and the potential for effectiveness and implementation in clinical practice. Quantitative and qualitative process evaluation data will be analysed to consider the following continuation criteria.

Successful uptake, recruitment, and retention.Successful implementation of the ExSCIP intervention.Process evaluation indicates that ExSCIP is acceptable to people with NP after SCI and to staff delivering the intervention.A positive effect on pain and pain interference outcomes are identified and are meaningful.

The intervention will be delivered in the Motion Analysis Laboratory at University College Dublin (UCD).

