### Outcomes

**
*Primary outcomes*
**

The primary outcomes will focus on trial feasibility. Full details of these and progression criteria to a multicentre, international RCT can be found in
Table 2:

**Table 2. T2:** Feasibility Outcomes and Progression Criteria.

Feasibility Outcomes	Progression Criteria
Number of individuals who contact researchers about the trial.	Successful intervention uptake, with recruitment rates of ≥35% of individuals deemed eligible following in-person assessment and at least 20 individuals randomised to the two arms.
Recruitment rates disaggregated by SII and NRH channels (recruitment capacity at named sites).	Loss to follow-up/attrition rates < 20%.
Number of individuals screened by phone.	Qualitative data that indicates that ExSCIP is an acceptable intervention to individuals with NP following SCI and to physiotherapists delivering the intervention, where no insurmountable barriers were identified.
Number of individuals who are eligible to proceed to in person-assessment following phone screening.	Safe implementation of the ExSCIP intervention: no serious adverse events
Number of individuals who consent to participate in the study following phone screening.	Average programme adherence of ≥ 80% of all sessions.
Trial uptake rates.	A non-inferior effect for NP intensity is observed in the intervention arm in comparison to the control arm.
Number who are eligible to participate in the study after in-person assessment.	A Minimal Clinically Important Difference (MCID) for NP intensity in an SCI population (1.74 points decrease on NRS) is observed within the 95% confidence interval for mean change for the intervention arm ( Farrar *et al*., 2001).
Number randomised to participate in the study.	
Adherence with the 12-week exoskeleton walking programme (attendance and total number of steps taken)	
Any safety/adverse events.	
Feasibility of stratified randomisation	
Number who are lost to follow up at week 13 and 6-month follow up.	
Feasibility of assessment procedures.	
Time needed to collect and analyse data.	

**
*Secondary outcomes*
**

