### Data/statistical analysis

Baseline demographics of group participants will be presented in two manners. Categorical data will be presented as frequencies & percentages. Continuous data will be presented as means & standard deviations. If there is evidence of skew in continuous data, mean and standard deviation (SD) will be substituted with median and interquartile range.

Outcome variables will be assessed at three time points (baseline, week 13, 6 month follow up). Health related quality of life (HRQoL) as assessed by the EQ-5D-5L will be converted from value scores to index scores for each item which will allow for calculation of a collated index score (
Hobbins *et al.*, 2018). Pain intensity, pain interference and HRQoL index scores will be presented as mean and SD at each time point. Within group mean differences and 95% confidence intervals (95% CI) will be calculated at week 13- and 6-month follow-up compared to baseline. Between group differences at each time point will be calculated using repeated measures ANOVAs. The effect sizes of between group differences will be assessed using ETA squared/Omega squared statistics. Statistical significance will be determined α-priori at an alpha level of 0.05. Statistical analysis will be undertaken using IBM SPSS version 29 (
IBM, 2023) and conducted as intention-to-treat and per-protocol. Alternatively, this statistical analysis can be performed using the open access R software (
R core team, 2024).

Exploratory EEG data analysis will use a multilevel linear mixed model (LMM) to examine differences between the intervention groups over time in the EEG alpha, beta and theta band power. Repeated measures within participants will be modelled as a random effect. Fixed effects in the model, will include group assignment and time. The moderating effects of pain intensity and interference will also be evaluated. The LMM will study both main effects and interaction effects using the R package lme4 (
Bates *et al.*, 2015) to fit the models. Models will be compared using Likelihood Ratio Tests (LRT) to assess the significance of effects.

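### Table 2's pain criteria do not require any benefit over control or any effect on pain interference, although the design section makes progression depend on a positive, meaningful effect on both

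*Protocol article*

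**What the plan says.** Four places in the protocol article bear on the pain criterion for progression.

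- **Background and rationale** says the trial will look for "positive signals in reduction of NP intensity and interference levels to warrant onward progression to a definitive trial".
- **Study design and setting** lists among the continuation criteria: "A positive effect on pain and pain interference outcomes are identified and are meaningful".
- **Outcomes, Table 2**, introduced as giving the criteria in full, has two pain rows. The first is "A non-inferior effect for NP intensity is observed in the intervention arm in comparison to the control arm". The second takes an MCID for NP intensity ("1.74 points decrease on NRS") and asks that it "is observed within the 95% confidence interval for mean change for the intervention arm". No row concerns pain interference.
- **Data/statistical analysis** states: "Between group differences at each time point will be calculated using repeated measures ANOVAs", with eta or omega squared as effect size, and "Statistical significance will be determined α-priori at an alpha level of 0.05". Confidence intervals are described only for within-group changes from baseline. Analyses are to be both intention-to-treat and per-protocol, without saying which decides progression.

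Under Sample size, randomisation, and blinding, the target is 20 per arm with at least 32 retained.

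**The concern.** A positive, meaningful effect and a non-inferior effect are different conditions. Two arms with the same mean change meet the second and not the first. Table 2 also drops interference, which the introduction and the design section both name.

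The MCID row does not restore the missing requirement. It looks at the intervention arm alone, so improvement over time that has nothing to do with the exoskeleton counts towards it. It asks only that the interval be wide enough to contain 1.74.

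The planned analysis does not settle what the first row means. A difference test at 0.05 and within-group intervals cannot establish non-inferiority. A non-significant ANOVA result shows only that a difference was not detected, and that becomes more likely as precision falls. At stake is the decision the trial exists to inform: following Table 2 could send the programme forward on data that the design section's own criterion would refuse.

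**Working it through.** The article gives no margin, SD or power figure, so there is nothing to reproduce. The following illustrates how the two pain rows behave.

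**Inputs.** 16 per arm: 32 retained, split evenly. MCID 1.74: Table 2. SD of change 2.2 NRS points, equal in both arms: an assumption, with 1.8 and 2.5 as the range. Normal data; two-sided 95% intervals.

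**Precision at SD 2.2.**
- Between-group half-width = t(0.975, 30) × 2.2 × √(2/16) = 2.042 × 0.778 = 1.59.
- Within-arm half-width = t(0.975, 15) × 2.2/√16 = 2.131 × 0.55 = 1.17.

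**One data set, two answers.** Suppose both arms show an observed mean fall of 1.0 point.
- MCID row: the interval is 1.0 ± 1.17, or −0.17 to 2.17. It contains 1.74, so the row passes, although the interval also contains zero.
- Non-inferiority row: the difference is 0, with interval −1.59 to 1.59. It passes as not significantly worse, as an observed estimate no worse, and against a margin of 1.74.
- Study design and setting: there is no positive effect against control, and interference has not been considered. The criterion is not met.

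**How often both pain rows pass** (simulation, 400,000 trials per scenario, SD 2.2; the MCID row read literally as 1.74 lying inside the interval):

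| True improvement, intervention / control | Not significantly worse | Observed estimate no worse | Margin 1.74 |
|---|---|---|---|
| 1 / 1 (no treatment effect) | 75% | 46% | 52% |
| 1 / 2 (intervention worse) | 66% | 10% | 14% |
| 0 / 0 | 16% | 14% | 14% |
| 0 / 1 | 16% | 6% | 7% |
| −1 / 0 (intervention arm deteriorates) | 0.4% | 0.3% | 0.3% |

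**Sensitivity to the SD**, same order of readings. For 1 / 1: 66%, 43%, 57% at SD 1.8 and 80%, 47%, 45% at SD 2.5. For 1 / 2: 55%, 6%, 19% and 72%, 13%, 12%. For 0 / 0: about 5% throughout at SD 1.8, and 26%, 22%, 20% at SD 2.5.

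**The non-inferiority row alone** (SD 2.2). With a true difference of 1 point against the intervention, a non-significant result has probability 76% (noncentral t, noncentrality 1/0.778). An observed estimate no worse has probability Φ(−1/0.778) = 10%.

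**The case against.** A reader might infer that an intervention 1 point worse than relaxation would usually be taken forward, since the non-inferiority row alone passes 76% of the time in that case. The documents do not support that as a statement about the decision. The 76% covers one row under one reading, and nothing in the article ties the ANOVA or the 0.05 level to that row. The wording that such an effect is observed equally suggests a point-estimate rule, which gives 10%. The MCID row also applies: when the intervention arm does not change and control improves by 1 point, the joint rate falls to 16% or less, and when the intervention arm deteriorates it is under 1%. The safety, adherence, retention and acceptability rows must be met as well.

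A reader might also call non-inferiority the wrong question because relaxation is an attention control. That label is not in the article, which describes an equally dosed relaxation programme and tells participants that two treatments are being compared.

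The missing margin is not a finding in itself, because it could stand in a full protocol or analysis plan that is not shown. Nor is a feasibility trial expected to be powered for efficacy.

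Finally, the MCID row can be read as Table 2's version of a meaningful effect on intensity, with the non-inferiority row as a comparative floor. That is a fair reading, but it still leaves no requirement for benefit over control and no interference criterion. A margin set elsewhere would not supply either.

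**Conclusion.** The point holds as a mismatch between the article's own statements of the pain criterion, and it should be fixed (SHOULD-FIX). The design section requires a positive and meaningful effect on pain and interference. Table 2 can be satisfied with equal arms and says nothing on interference, and the analysis described cannot show non-inferiority.

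The size depends on which reading applies and on whether the intervention arm improves at all. The problem is material when both arms improve somewhat, as in the 1 / 1 scenario, and is small when the intervention arm stays flat or deteriorates. All the probabilities rest on an assumed SD and assumed true changes; the textual mismatch rests on neither. The fault is in the decision rule and not in the sample size. Data collection, randomisation and participant safety are unaffected.

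**What to change.** In Table 2, replace the non-inferiority row with a criterion that matches the design section, for example: the baseline-adjusted between-group difference at week 13, by intention-to-treat, favours ExSCIP for NP intensity and for pain interference, reported with 95% confidence intervals and read alongside the MCID row.

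In Data/statistical analysis, add this between-group estimate and its interval for both outcomes. State that it informs the progression decision and is not a test at 0.05. Settle the wording before any unblinded results are seen, as the study is under way.

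The cost is an edit to two sections, not to Table 2 alone, with no extra participants or data. The pain criterion becomes somewhat harder to meet. A rule that the estimate favours ExSCIP remains weak evidence: with truly equal arms it passes about half the time for intensity alone. It should therefore be read with its interval and not as proof of benefit.

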### Sample size, randomisation, and blinding

As ExSCIP is a feasibility trial, a sample size calculation will not be conducted. The trial aims to recruit 20 participants to the intervention arm and 20 to the control arm, retaining at least 32 at follow-up. Due to practical considerations including traumatic SCI being a rare condition in Ireland, the strict eligibility criteria in addition to the precedent set by previous RCT’s in this area with considerably smaller sample sizes (
Martinez *et al.*, 2018), this number is considered adequate to inform whether sufficient participants can be recruited and retained in the study and to evaluate the feasibility goals outlined.

Following informed consent and baseline evaluation for exoskeleton, recruited participants will then be randomly allocated to the intervention group (ExSCIP) or to the comparator group (receiving a blended relaxation programme devoid of motor imagery). This will be completed by an independent gatekeeper based in the UCD Centre for Support and Training in Analysis and Research (CSTAR), using a pre-generated electronic randomisation schedule stratified by NP severity. Allocation disclosure will be made by telephone by the independent gatekeeper in CSTAR to the trial interventionist after informed consent and baseline evaluation.

To minimise potential biases, all assessments and outcome measures (baseline, post intervention and 6-month follow-up) will be taken by an independent assessor blinded to the treatment allocation. The data analyst will also be blinded to the intervention allocation.

Blinding participants to the ExSCIP intervention is not feasible. The hypothesis of the study will be masked however in the information to subjects. Participants will be informed that the trial is comparing two types of treatment, to avoid higher expectations in the ExSCIP group.

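### The MCID progression row is met only if 1.74 lies inside the ExSCIP arm's own 95% CI, so read literally it fails a clearly larger benefit and becomes easier to meet as the CI widens

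*Protocol article*

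**What the plan says.** Table 2 (Outcomes, Primary outcomes) lists the feasibility outcomes and the progression criteria. Two criteria concern pain. One is "A non-inferior effect for NP intensity is observed in the intervention arm in comparison to the control arm", with no margin given. The other sets the MCID at "1.74 points decrease on NRS" and requires that this value "is observed within the 95% confidence interval for mean change for the intervention arm".

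Data/statistical analysis shows which interval is meant: "Within group mean differences and 95% confidence intervals (95% CI) will be calculated at week 13- and 6-month follow-up compared to baseline". It is a within-arm change from baseline, calculated at two time points, and the Table 2 row does not say which one decides.

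Study design and setting gives the continuation criterion that the row should serve: "A positive effect on pain and pain interference outcomes are identified and are meaningful".

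On size, the protocol states: "The trial aims to recruit 20 participants to the intervention arm and 20 to the control arm, retaining at least 32 at follow-up". It also states: "As ExSCIP is a feasibility trial, a sample size calculation will not be conducted". No SD of change is given.

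**The concern.** A rule that a value must lie within an interval has two ends. It fails when the interval falls short of 1.74, as intended, and also when the interval lies wholly beyond 1.74. The second case is strong evidence of a benefit larger than the MCID, yet the row would record it as not met.

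The row sets no condition on the point estimate, the lower limit or the width of the interval. Fewer completers or noisier scores widen the interval and make it more likely to cover 1.74.

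The row also looks at one arm only. Any improvement that both arms share counts towards it.

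The row is the only numerical test in the protocol of whether the pain effect is meaningful, and it feeds the decision on a multicentre, international trial.

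**Working it through.** **Inputs.** The threshold is 1.74 (Table 2). Completers in the ExSCIP arm: 32 retained / 2 arms = 16, or 20 with no loss (Sample size, randomisation, and blinding). The SD of change is not in the protocol; I assume 2.0 NRS points, with a range of 1.5 to 3.0. Changes are taken as normal and the 95% CI as two-sided. The protocol states no operating characteristic for this row, so there is no figure to reproduce.

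**Pass window.** The CI is mean reduction ± h, with h = t(0.975, n−1) × SD / √n. The row is met if the mean reduction lies between 1.74 − h and 1.74 + h.

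- n = 16, SD 2.0: h = 2.131 × 2.0 / 4 = 1.07, so the window is 0.67 to 2.81.
- n = 20, SD 2.0: h = 2.093 × 2.0 / 4.472 = 0.94, so the window is 0.80 to 2.68.
- n = 16, SD 2.5: h = 2.131 × 2.5 / 4 = 1.33, so the window is 0.41 to 3.07.

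An observed mean reduction above the upper end does not meet the row. The window grows with the SD and shrinks with n.

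**Probability of meeting the row.** T = (mean − 1.74) / (s/√n) follows a noncentral t distribution with n − 1 degrees of freedom and noncentrality (μ − 1.74) / (SD/√n), where μ is the true mean reduction. The row is met when |T| ≤ t(0.975, n−1). At n = 16 and SD 2.0, SD/√n = 0.5, so μ = 3.0 gives noncentrality 1.26 / 0.5 = 2.52 and μ = 0.5 gives −1.24 / 0.5 = −2.48. The rule responds only to the distance from 1.74, so these two truths are treated almost alike. Simulation with 200,000 replicates per cell agrees to within a percentage point.

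| True mean reduction | Row as written, n=16, SD 2.0 | Upper limit ≥ 1.74, n=16, SD 2.0 |
|---|---|---|
| 0 | 10% | 10% |
| 0.5 | 36% | 36% |
| 1.74 | 95% | 97.5% |
| 3.0 | 35% | about 100% |
| 3.5 | 9% | about 100% |

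**Sensitivity of the row as written.** At n = 16, over SD 1.5 to 3.0, the probability is 1% to 42% at no true change and 12% to 65% at a true 3.0. At n = 20 and SD 2.0 it is 4% at no true change and 24% at 3.0.

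**Shared improvement.** If both arms improved by a true 1.5 points, the row would be met about 93% of the time (n = 16, SD 2.0) with no difference between treatments.

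**Would moving the rule to the between-group CI help?** The unadjusted half-width at 16 per arm and SD 2.0 is t(0.975, 30) × 2.0 × √(2/16) = 2.042 × 0.707 = 1.44. With no true difference, an interval that wide reaches 1.74 about a third of the time (about 33%), and about 24% of the time at 20 per arm. The null differs (no between-arm difference rather than no within-arm change), and baseline adjustment would narrow the interval somewhat, but imprecision would still be rewarded.

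**The case against.** The best defence is intent. The authors probably meant that the MCID should not be ruled out, and a reader who knows this would not penalise an interval lying beyond 1.74. That is plausible, but the row does not say it, and that reading removes only the upper-end fault.

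Several stronger readings are tempting and go too far.

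- *The progression decision ignores the control arm.* A reader might infer this, but the adjacent row does compare the arms. What stands is narrower: that row has no margin, and non-inferiority to relaxation does not show that a benefit is meaningful.
- *The row can on its own stop an effective intervention.* Study design and setting presents the criteria as matters to be considered together, with qualitative data. Nowhere is one failed row a veto.
- *High dropout would carry the trial through.* Table 2 separately requires attrition below 20%, which limits that route. It does not limit noisy scores.
- *The chance of a false pass is very high because only 10 may be in the arm.* At n = 10 and SD 2.0 the row is met 31% of the time with no true change. That depends on reading "at least 20 individuals randomised to the two arms" as a total, whereas the recruitment aim is 20 per arm, where the figure is 4%.
- *Regression to the mean is built in because the qualifying score is also the baseline score.* The screening section confirms the NRS at Stage 2 and collects the full pain data set at Stage 3. It does not say that one score serves both purposes.

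**Conclusion.** The concern holds for this row as written. Its upper end contradicts the protocol's own criterion of a positive and meaningful effect. With 16 completers and an assumed SD of 2.0, a true 3.0-point reduction meets the row about as often as a true 0.5-point one (35% against 36%), and a true 3.5 about as often as no change (9% against 10%). The percentages rest on the assumed SD; the direction of each fault does not.

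The row also rewards imprecision and uses no control-arm quantity. Both are weaknesses of the row, not of the whole progression set. Pain is a secondary outcome here and the criteria are weighed together, so this is a should-fix. Whether 1.74 is the right MCID rests on a cited source that is not at hand and was not assessed.

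**What to change.** Reword the row now; the study is ongoing, so this should be done before outcome data are seen. Suggested text: *The upper limit (largest reduction) of the 95% CI for mean reduction in NRS pain intensity at week 13 in the ExSCIP arm is at least 1.74 points; an interval lying wholly beyond 1.74 also meets the criterion.* This settles the time point and raises the probability at a true 3.0 from 35% to about 100% (n = 16, SD 2.0).

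Add two things:

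- State that the row is a permissive signal check, meaning that the MCID has not been ruled out. A wide interval still helps it pass: the 10% at no true change and 36% at 0.5 are unaltered.
- Report the baseline-adjusted between-group difference with its 95% CI beside the row, so that improvement common to both arms is not read as benefit.

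Do not make coverage of 1.74 by the between-group CI the pass rule, because of the pass rates under no true difference shown above.

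The cost is one reworded row and one extra reported estimate, with no new data. That estimate will be imprecise: a half-width of about 1.4 points at 16 per arm (SD 2.0, unadjusted).
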